## Abstract

**Background:**

Clinical evidence in coronary surgery is usually derived from retrospective, single institutional series. This may introduce significant biases in the analysis of critical issues in the treatment of these patients. In order to avoid such methodological limitations, we planned a European multicenter, prospective study on coronary artery bypass grafting, the E-CABG registry.

**Design:**

The E-CABG registry is a multicenter study and its data are prospectively collected from 13 centers of cardiac surgery in university and community hospitals located in six European countries (England, Italy, Finland, France, Germany, Sweden). Data on major and minor immediate postoperative adverse events will be collected. Data on late all-cause mortality, stroke, myocardial infarction and repeat revascularization will be collected during a 10-year follow-up period. These investigators provided a score from 0 to 10 for any major postoperative adverse events and their rounded medians were used to stratify the severity of these complications in four grades. The sum of these scores for each complication/intervention occurring after coronary artery bypass grafting will be used as an additive score for further stratification of the prognostic importance of these events.

**Discussion:**

The E-CABG registry is expected to provide valuable data for identification of risk factors and treatment strategies associated with suboptimal outcome. These information may improve the safety and durability of coronary artery bypass grafting. The proposed classification of postoperative complications may become a valuable research tool to stratify the impact of such complications on the outcome of these patients and evaluate the burden of resources needed for their treatment.

**Clinical Trials number:**

NCT02319083

## Background

Myocardial revascularization is the most common cardiac surgical procedure. Although the efficacy and long-term durability of coronary artery bypass grafting (CABG) over percutaneous coronary intervention (PCI) has been largely proved in a number of subsets of patients [1, 2], PCI along with its related technological advances has slowly become the most common invasive treatment method for coronary artery disease. The minimally invasive nature and the low risk of immediate adverse events are strong arguments in favor of PCI. However, the current durability of PCI is most likely inferior to that of CABG, particularly in patients with multivessel disease [1, 2], diabetes [2, 3] and renal failure [4].

Contrary to PCI, advancements in coronary surgery during the last decade have been slow and limited to improvements in perfusion and anesthesiological methods. Furthermore, clinical evidence in CABG is usually derived from retrospective and single institutional series and this may introduce significant biases in the analysis of critical issues in the treatment of these patients. However, since CABG is a major surgical procedure associated with postoperative mortality and significant morbidity, there is a need of improvements in the treatment of patients undergoing coronary surgery in order to reduce the risk of early and late adverse events. Prospective analyses of the impact of baseline risk factors, operative techniques, perioperative treatment methods and secondary prevention strategies on the outcome of patients undergoing surgical revascularization of the myocardium are expected to provide valuable and reliable information to improve the safety and durability of CABG.

### Rationale of the study

Improvements in the surgical treatment of cardiac diseases are possible only when implementation of current methods and development of new methods are based on the solid ground of large and reliable clinical data [5]. Knowledge on these issues can be generated by clinical prospective registries. The rationale of this European multicenter study on patients undergoing isolated CABG (E-CABG) is therefore to collect in a prospective fashion current data on baseline characteristics, operative and anesthesiological methods and postoperative outcome of patients undergoing CABG in several European centers of cardiac surgery.

Prospective clinical registries have a relevant role in clinical research as they differ from randomized clinical trials in many aspects. They require less resources and are not narrowly focused on specific subsets of patients, but rather provide data on general patient populations with limited exclusion criteria. Importantly, clinical registries may provide data on long-term outcome that exceed the study window of a trial [5]. Clinical findings of registries assume even more significance when including study populations from different geographic areas with heterogeneous referral pathways, baseline clinical characteristics and perioperative treatment strategies.

The E-CABG has been planned to provide data with well-defined definition criteria and this paper is a summary of baseline, operative and postoperative variables. In particular, these investigators propose a grading system to stratify the severity of postoperative complications in patients undergoing adult cardiac surgery. This study is registered in Clinicaltrials.gov with the number NCT02319083.

## Methods

### Setting, design, study population, patient recruitment and study period

The E-CABG is an observational registry study and its data are prospectively collected consecutively from 13 centers of cardiac surgery of either university or community hospitals located in six European countries (England, Finland, France, Germany and Italy) (Table 1). Patients aged > 18 years undergoing isolated primary or redo CABG for stable coronary artery disease or acute coronary syndrome are eligible for inclusion in this prospective registry. Patients undergoing any other major cardiac surgery procedure will be excluded from this registry. However, patients who undergo CABG associated with Maze will be included in this registry. Patients are recruited in a consecutive series from each institution and their data collected in a specifically created Access-datasheet. The minimum recruitment period is 12 months (January 1 - December 31, 2015). Patients will be followed up after surgery for the following 10 years.

**Table 1 Tab1:** Participating centers and steering committee members of the E-CABG multicenter trial

	*Participating centers*	*Steering Committee Member*	*Other Investigators*
1	Department of Surgery, Oulu University Hospital, Oulu, Finland	[name], *Principal investigator*	[name]
			[name]
2	Department of Cardiac Surgery, Verona University Hospital, Verona, Italy	[name]	[name]
3	Division of Cardiac Surgery, Ospedali Riuniti di Trieste, Trieste, Italy	[name]	[name]
			[name]
4	Cardiac Surgery Unit, Ferrarotto Hospital, University of Catania, Catania, Italy	[name]	[name]
5	Department of Cardiac Surgery, Klinikum Nürnberg, Paracelsus Medical University, Nuremberg, Germany	[name]	[name]
6	Department of Cardiac Surgery, Leicester University Hospital, Leicester, UK	[name]	[name]
			[name]
7	Department of Thoracic and Cardio-Vascular Surgery, University Hospital Jean Minjoz, Besançon, France	[name]	[name]
8	Department of Molecular Medicine and Surgery, Department of Cardiothoracic Surgery and Anesthesiology, Karolinska Institutet, Karolinska University Hospital, Stockholm, Sweden	[name]	[name]
9	Unit of Cardiac Surgery, Department of Cardiosciences, Hospital S. Camillo-Forlanini, Rome, Italy	[name]	[name]
10	Division of Cardiothoracic and Vascular Surgery, Pontchaillou University Hospital, Rennes, France	[name]	[name]
			[name]

### Data management and monitoring

Data will be collected in to a dedicated Access datasheet with predefined variables. Data including patients’ codes are stored in institutional network and secured by access code. Each Steering Committee Member is in charge for checking the quality and validity of her/his institution’s dataset. Auditing of the dataset will be performed every six months at institutional level by checking the data of 10 % of patients. Data without any patient identification code will be submitted to the principal investigator for further data checking and merging. The merged and checked dataset will be available to all E-CABG investigators for subanalyses.

### Statistical methods

Continuous variables will be reported as mean and standard deviation or median and interquartile range as needed. Dichotomous and nominal variables will be reported as counts and percentages. Missing data will not be replaced. Univariate analysis will be performed using the Mann–Whitney *U* test, Student’s *t*-test, Kruskall-Wallis test, Wilcoxon test, Fisher exact test, Chi-square test and Kaplan-Meier test. Multivariable analyses will be performed using logistic, classification tree, linear and ordinal regression methods as well as the Cox-proportional hazards method. Significant differences between study groups will be adjusted by using propensity score as covariate or one-to-one propensity score matching. Matching will be performed using a caliper width of 0.2 of the standard deviation of logit of the propensity score. Multiple propensity score adjusted analysis will be performed in case of multiple study groups. A Bayesian hierarchical approach will be used in case of significant between-centers variability.

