### Immediate and late outcome end-points

The primary outcome end-points will be defined according to the issue investigated in each study. The main immediate outcome end-points of studies from the E-CABG registry are: 1) In-hospital mortality and 30-day mortality, 2) stroke, 3) prolonged use of inotropes, 4) postoperative need of intra-aortic balloon pump (IABP) or extracorporeal mechanical oxygenation (ECMO), 5) immediate repeat revascularization, 6) wound infection and mediastinitis, 7) blood losses and use of blood products, 8) nadir hematocrit, 9) use of prothrombotics, 10) resternotomy for bleeding, 11) atrial fibrillation, 12) acute kidney injury and need of renal replacement therapy, 13) type V myocardial infarction, 14) pericardial effusion requiring treatment, 15) postoperative use of antibiotics, 16) delirium requiring drug treatment, 17) length of stay in the intensive care unit, and 18) length of in-hospital stay. The late outcome end-points of studies from the E-CABG registry are: 1) all-cause mortality, 2) cardiovascular mortality, 3) stroke, 4) myocardial infarction, 5) repeat revascularization and 6) a combined outcome end-point including any of these late adverse events. These end-points and their definition criteria are described in details in the following paragraphs of this article.

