#### Late stroke

This refers to any focal or global neurological syndrome occurring after discharge and caused by ischemia and/or hemorrhage not resolving within 24 h. The diagnosis and nature of stroke is made on the basis of findings at computed tomography and/or magnetic resonance imaging of the brain and confirmed by a neurologist.

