#### Late myocardial infarction

This refers to any myocardial infarction occurring after discharge and requiring medical or revascularization treatment. Since the current definition of type V myocardial infarction requires adequate validation, only myocardial infarction occurring after discharge will be considered as late myocardial infarction.

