#### Late repeated revascularization

This refers to any CABG and/or PCI performed after discharge for graft and/or stent-related complication as well as for progression of coronary artery disease.

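### Kaplan-Meier and Cox are the only time-to-event methods named; if one minus Kaplan-Meier is reported as the 10-year risk of stroke, MI, repeat revascularization or cardiovascular death, that risk is overstated

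*Protocol article*

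**What the plan says.** The Statistical methods section of the protocol article is a general list meant to serve all studies from the registry. Its univariate part closes with "Fisher exact test, Chi-square test and Kaplan-Meier test", and its multivariable part with "linear and ordinal regression methods as well as the Cox-proportional hazards method". No other time-to-event method is named, and competing risks and cumulative incidence are not mentioned anywhere.

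The section on immediate and late end-points lists six late outcomes: "1) all-cause mortality, 2) cardiovascular mortality, 3) stroke, 4) myocardial infarction, 5) repeat revascularization and 6) a combined outcome end-point". On duration, the design section says "Patients will be followed up after surgery for the following 10 years".

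Three of the late outcomes are defined without death as part of the event:

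- Late stroke: "This refers to any focal or global neurological syndrome occurring after discharge and caused by ischemia and/or hemorrhage not resolving within 24 h".
- Late MI: "This refers to any myocardial infarction occurring after discharge and requiring medical or revascularization treatment".
- Late repeat revascularization: "This refers to any CABG and/or PCI performed after discharge for graft and/or stent-related complication".

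The definition of late death adds that causes of death are collected, so that cardiovascular deaths can be told apart. The combined end-point counts death from any cause as an event.

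**The concern.** A patient who has died cannot later have a stroke, an infarction or a repeat revascularization, and a patient who has died of a non-cardiovascular cause cannot die of a cardiovascular one. Kaplan-Meier has only two states, so it must treat such deaths as censoring. One minus Kaplan-Meier then estimates the risk that would apply if the competing deaths did not happen. It does not estimate the proportion of operated patients who have the event.

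The durability of coronary bypass surgery is a stated interest of the registry, and the late event risks are how durability would be described. Over 10 years of follow-up, in a cohort with no upper age limit, competing deaths can be numerous enough to matter. Because the methods list is shared by many sub-studies, the choice would carry over from one publication to the next.

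**Working it through.** **Inputs.** From the protocol article: the late end-points, their definitions and the 10-year horizon. The article gives no event rate or mortality rate, so there is no figure of its own to reproduce. All hazards below are assumptions, shown as a range.

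**Formulas.** Let *a* be a constant event hazard, *m* a constant hazard of competing death, and T = 10 years.

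- One minus Kaplan-Meier, deaths censored: 1 − exp(−aT).
- Cumulative incidence: a/(a+m) × [1 − exp(−(a+m)T)].

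**Direction.** Both quantities add up the event hazard over time. Kaplan-Meier weights it by the probability of no event so far. Cumulative incidence weights it by the probability of no event and no competing death so far. The second weight is never larger, so one minus Kaplan-Meier is too high whenever competing deaths precede later events. This does not depend on the hazards chosen.

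**Size under assumed annual hazards.**

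- a = 0.015, m = 0.03 (1 − exp(−0.30) = 25.9% competing mortality at 10 years): 1 − exp(−0.15) = 13.9%, against 0.015/0.045 × (1 − exp(−0.45)) = 12.1%. Relative excess 15%.
- a = 0.015, m = 0.04 (1 − exp(−0.40) = 33.0% competing mortality): 13.9%, against 0.015/0.055 × (1 − exp(−0.55)) = 11.5%. Relative excess 21%.
- a = 0.03, m = 0.04: 1 − exp(−0.30) = 25.9%, against 0.03/0.07 × (1 − exp(−0.70)) = 21.6%. Relative excess 20%.

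**Wider range.** Hold one minus Kaplan-Meier at 10% at 10 years and vary the assumed competing mortality:

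| Competing mortality at 10 years | Cumulative incidence | Relative excess of one minus Kaplan-Meier |
|---|---|---|
| 10% | 9.50% | 5% |
| 20% | 8.98% | 11% |
| 30% | 8.44% | 19% |
| 40% | 7.87% | 27% |
| 50% | 7.26% | 38% |

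With one minus Kaplan-Meier between 5% and 20%, and competing mortality between 10% and 50%, the excess runs from 0.25 to 5.4 percentage points.

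**Check by simulation.** With 400,000 simulated patients, 30% competing mortality and 10% event risk in the absence of death, one minus Kaplan-Meier was 10.0% and the actual proportion with the event 8.5% (formula 8.44%).

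**End-points not affected.** All-cause death has no competing death. For a composite that counts all-cause death, the same scenario gives 1 − 0.7 × 0.9 = 37.0% by Kaplan-Meier and 37.1% observed in the simulation, so there is no bias.

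**Comparisons between groups.** The expression 1 − exp(−aT) does not contain *m*. Two groups with the same event hazard but different mortality (m = 0.03 and m = 0.04) have the same Kaplan-Meier curve, 13.9% at 10 years, while their cumulative incidences differ (12.1% and 11.5%).

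**The case against.** The strongest reply is that the methods section is a generic list that assigns no method to any end-point. Kaplan-Meier and Cox are correct for two of the six late outcomes, so naming them is no error. Kaplan-Meier stands among univariate tests and is called a test, which most naturally means a log-rank comparison of curves, and nothing says that one minus Kaplan-Meier will be reported as absolute risk. Primary end-points are set study by study and the Steering Committee reviews each study plan, so competing death could be handled there.

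Much of this stands. A reader might infer that the protocol prescribes Kaplan-Meier for late stroke, MI, revascularization and cardiovascular death. It does not say so. The link is an inference from the absence of any other univariate time-to-event method, and the point is therefore conditional.

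A reader might also infer that group comparisons with deaths censored are invalid, or that Kaplan-Meier curves would diverge for groups that differ only in mortality. Neither holds. Log-rank and Cox with deaths censored compare cause-specific hazards validly. With equal event hazards and independent censoring the Kaplan-Meier curves coincide; it is cumulative incidence, and with it Gray's test, that responds to mortality.

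Nor do the documents declare particular patient groups, such as frail or elderly patients, as subgroups of interest in which the bias would matter most.

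What does not stand is that this is merely detail left for later. The section is specific enough to fix a matching caliper, and the time-to-event estimator it names does not give absolute risk for four of the six late end-points it is meant to serve.

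**Conclusion.** The point holds in conditional form. If one minus Kaplan-Meier is used to report the absolute risk of late stroke, MI, repeat revascularization or cardiovascular death, the incidence is overstated. The direction is certain once competing deaths occur. The size cannot be derived from the documents: the relative excess is 15% to 21% in the three assumed-hazard examples, and about 5% to 38% when assumed competing mortality runs from 10% to 50%. These figures rest on constant hazards. All-cause death and the combined end-point are unaffected, and so is the validity of log-rank and Cox as cause-specific comparisons. The plan should be amended because the better method is standard, cheap and feasible with the data already collected.

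**What to change.** Amend the Statistical methods section so that:

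- For late stroke, MI and repeat revascularization, absolute risk is reported as Aalen-Johansen cumulative incidence with death as the competing event. For cardiovascular mortality the competing event is non-cardiovascular death.
- Log-rank and Cox results for these four end-points are labelled as cause-specific.
- Gray's test or a Fine-Gray model is used only where a difference in absolute risk is the question, with a note that these also reflect differences in mortality between groups.
- Kaplan-Meier with the log-rank test is kept for all-cause death and the combined end-point. This also replaces the loose term Kaplan-Meier test, since Kaplan-Meier is an estimator.

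The cost is one or two sentences, standard software and no new data, because deaths and their causes are already recorded. The downside is a little more analysis work and two kinds of estimate, cause-specific hazards and cumulative incidence, to explain to readers.

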The E-CABG investigators have selected 25 complications or interventions for their treatment (Table 10), which are believed to have a prognostic impact and possibly associated with increased resources for their treatment. These investigators recognized that in many cases, an intervention performed for any complication would provide a better stratification measure than considering the complication itself. Because of this, a number of complications are herein defined as any intervention performed for their specific treatment. These investigators decided to not enlist here some postoperative adverse events because of intrinsic difficulties in defining their true nature (for example: pneumonia, type V myocardial infarction, sepsis), because they are secondary to other more significant adverse events (for example: prolonged tracheal intubation) or any time interval may not capture the real extent of the event (for example: postoperative blood losses). These investigators recognized also the difficulty in identifying a valid definition of postoperative low-cardiac output syndrome. In fact, thermodilution catheter is not routinely used in many centers and the use of a cutoff of postoperative cardiac index to define this event is thus not feasible. Furthermore, postoperative use of inotropes varies significantly between institutions as their use after cardiac surgery is not limited to the treatment of markedly decreased cardiac index. Therefore, in this registry the definition of postoperative severely depressed cardiac function is reserved only to those conditions requiring postoperative insertion of IABP or ECMO.

**Table 10 Tab10:** Mean, median and interquartile range of score assigned by 24 cardiac surgeons to 25 significant postoperative complications or interventions for their treatment

*Postoperative complication or intervention*	*Mean score*	*Median score*	*Interquartile range*
Transfusion of 1 unit of RBC	0.5	0.5	1.0
Transfusion of 2–4 units of RBC	2.7	2.5	1.0
Transfusion of 5–10 units of RBC	5.2	5.0	2.0
Transfusion of > 10 units of RBC	7.2	7.0	1.0
Reoperation for bleeding	4.6	5.0	1.75
Transfusion of platelets	2.7	2.0	1.75
Transfusion of fresh frozen plasma or Octaplas	2.7	3.0	1.75
Pericardial effusion requiring pericardial fenestration	3.9	4.0	1.0
Postoperative use of antibiotics	1.9	2.0	1.0
Atrial fibrillation	2.3	2.0	2.0
Ventricular fibrillation/asystole	6.8	8.0	3.0
Administration of inotropics > 12 h	3.9	4.0	2.0

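### Propensity-score adjustment and centre modelling are made to depend on a significance test, which can miss real imbalance in small sub-studies and real centre differences for rare outcomes

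*Protocol article*

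**What the plan says.** Two sentences in the Statistical methods section of the protocol article matter here. On confounding: "Significant differences between study groups will be adjusted by using propensity score as covariate or one-to-one propensity score matching". On centre: "A Bayesian hierarchical approach will be used in case of significant between-centers variability". Both come after a list of univariate tests, so statistical significance is the natural reading, although no alpha is given.

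The same section plans regression without any trigger: "Multivariable analyses will be performed using logistic, classification tree, linear and ordinal regression methods as well as the Cox-proportional hazards method". It does not say how covariates are chosen for those models or whether centre is among them.

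Elsewhere the article expects centres to differ. Rationale of the study values a registry drawn from "different geographic areas with heterogeneous referral pathways, baseline clinical characteristics and perioperative treatment strategies". The section classifying the severity of complications states that "postoperative use of inotropes varies significantly between institutions". There are 13 centres. Under Data management and monitoring the merged data are opened to all investigators for sub-analyses, and for end-points "The primary outcome end-points will be defined according to the issue investigated in each study". The size of a sub-study and the rarity of its outcome can therefore vary widely.

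**The concern.** Confounding depends on how far the groups differ on a variable and on how strongly that variable predicts outcome. A baseline p-value mixes the first of these with sample size and carries no information on the second. Used as a gate, it can pass over a strong confounder in a small comparison and react to a trivial difference in a large one.

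The centre rule has a parallel weakness. Patients in one centre share referral patterns and practice, so centre may act both as a confounder and as a clustering unit. Whether it is modelled should not depend on a heterogeneity test over 13 units that has little power when events are few. Because that test is run on the outcome, centre could be modelled for one end-point and ignored for another within the same comparison.

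At stake are residual confounding in the propensity-score comparisons and, where the exposure tracks centre, standard errors that are too small.

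**Working it through.** The article gives no sample size, alpha, event rate or between-centre variance, so there is no figure of its own to reproduce. Only the 13 centres come from the document. Every other input below is an assumption.

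**Baseline test, variables screened one by one.** Assume a true standardized difference d = 0.25, n per group, and a two-sided 5% z-test. The test statistic has mean m = d × √(n/2). The probability of a non-significant result is Φ(1.96 − m) − Φ(−1.96 − m).

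- n = 100: m = 0.25 × √50 = 1.768; probability = Φ(0.192) − Φ(−3.728) = 0.576.
- n = 200: m = 0.25 × √100 = 2.5; probability = Φ(−0.54) − Φ(−4.46) = 0.295.

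The mean observed difference among missed cases is that of a normal variable truncated to ±1.96, multiplied by √(2/n). It is 0.15 for n = 100 and 0.13 for n = 200. If the variable has an assumed outcome log-odds ratio of 0.7 per SD and nothing else adjusts for it, the spurious odds ratio at n = 100 is about exp(0.7 × 0.154) = 1.11.

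A binary confounder gives a similar picture. At 30% against 20%, it is flagged with probability 0.21, 0.37, 0.64 and 0.91 for 50, 100, 200 and 400 per group; 294 per group are needed for 80%.

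**Centre test.** Simulate 13 equal centres with normal centre effects on the logit scale, and apply a chi-square test of homogeneity on 12 degrees of freedom at 5%. With 200 patients per centre (2,600 in all) and a 2% outcome, the test is non-significant in:

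- about 78% of datasets at SD 0.3;
- about 42% of datasets at SD 0.5.

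Common outcomes fare much better. At 30% events and the same size, the test detects the variation in 97% (SD 0.3) and over 99% (SD 0.5) of datasets.

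**Consequence of a missed centre test.** Take an exposure set wholly by centre (7 centres against 6) with no true effect, and compare the groups ignoring centre. Among datasets where the heterogeneity test was non-significant, type I error at 2,600 patients and 2% events is about 0.06-0.07 (SD 0.3) and 0.08-0.09 (SD 0.5), against a nominal 0.05. At 10% events and SD 0.3 it is about 0.09-0.10, but there the test misses in only about 22% of datasets.

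**The case against.** **Regression is planned without a trigger.** A reader might infer that confounders are adjusted for only when a test flags them. The article does not support this, because a confounder missed at baseline may still enter a multivariable model. This stands and limits the point to the propensity-score comparison and the centre model. It does not remove the point, since no covariate rule is stated for those regressions that would offset the trigger. The odds ratio of 1.11 applies only where no such regression adjusts for the variable.

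**Screening variable by variable is one reading.** The sentence could also mean that, once groups differ on anything, a full propensity score is built. Then the trigger fails only if nothing is flagged. With five independent covariates, each at 0.25 and 100 per group, that is 0.576^5, or about 6%; with ten, about 0.4%. Correlated or less imbalanced covariates would raise these figures. The wording does not settle which reading is meant, so 58% is conditional on screening.

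**Outcome rarity.** It is tempting to say that rare outcomes weaken both triggers. They weaken only the centre test; a baseline test does not involve the outcome.

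**Centre-level exposure is assumed.** The article does not say that operative technique or other treatments are set by centre. It records technique for each procedure and defines off-pump experience by surgeon. Its remark on inotropes explains why a definition was narrowed. A claim that all intervals are too narrow is therefore not supported; the inflation applies to exposures that vary largely by centre, and it is modest.

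**Detail may sit in sub-study plans.** The Steering Committee reviews a plan for each proposal, and covariate lists belong there. That is fair, but the two triggers are stated rules in this document, and a sub-study plan that followed them would inherit the weakness.

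**Conclusion.** The point holds in a limited form. Statistical significance is the stated trigger for propensity-score adjustment and for modelling centre, and it is a poor trigger for both. The centre rule is the clearer fault: it is unambiguous, it makes modelling wait for a test although the article already expects centres to differ, and for a 2% outcome the test would miss real variation in roughly 42% to 78% of datasets. The resulting type I error, about 0.06-0.09, is a modest inflation and presumes an exposure that follows centre. The baseline rule could miss a 0.25 standardized difference in about 58% (100 per group) or 29% (200 per group) of comparisons, if screening is by single variables. All these sizes rest on assumed sample sizes, event rates and centre variances. They illustrate the weakness of the rule and do not predict what any sub-study will show.

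**What to change.** In Statistical methods, reword the two sentences to remove both significance triggers.

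- For each sub-study, choose the propensity-score covariates in advance on clinical grounds from variables already collected, for example EuroSCORE II items, urgency and frailty, whatever their p-values. Leave out the exposure under study; for that reason one fixed list cannot serve every sub-study.
- Judge balance by standardized differences, not by tests.
- Account for centre in every comparative model, for example by a random intercept or by putting centre in the propensity model, whatever the heterogeneity test shows.

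The cost is two reworded sentences, a little more modelling and slightly wider intervals. No new data are needed.
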